## Abstract

**Background:**

Cancer survivorship in Ireland is increasing in both frequency and longevity. However, a significant proportion of cancer survivors are overweight. This has negative implications for long-term health outcomes, including increased risk of subsequent and secondary cancers. There is a need to identify interventions, which can improve physical and psychological outcomes that are practical in modern oncology care. Mobile health (mHealth) interventions demonstrate potential for positive health behavior change, but there is little evidence for the efficacy of mobile technology to improve health outcomes in cancer survivors.

**Objective:**

This study aims to investigate whether a personalized mHealth self-management lifestyle program is acceptable to participants and can improve physical and psychological outcomes of a subgroup of cancer survivors with increased health risks related to lifestyle behaviors.

**Methods:**

A sample of 123 cancer survivors (body mass index >25 kg/m^2^) was randomly assigned to the control (n=61) or intervention (n=62) group. The intervention group attended a 4-hour tailored lifestyle information session with a physiotherapist, dietician, and clinical psychologist to support self-management of health behavior. Over the following 12 weeks, participants engaged in personalized goal setting to incrementally increase physical activity (with feedback and review of goals through short message service text messaging contact). Objective measures of health behavior (ie, physical activity) were collected using Fitbit (Fitbit, Inc). Data on anthropometric, physiological, dietary behavior, and psychological measures were collected at baseline (T0), 12 weeks (T1; intervention end), and 24 weeks (T2; follow-up). Semistructured interviews were conducted to explore the retrospective acceptability of the Moving On program from the perspective of the recipients.

**Results:**

This paper details the protocol for the Moving On study. The project was funded in August 2017. Enrolment started in December 2017. Data collection completed in September 2018. Data analysis is underway, and results are expected in winter 2019.

**Conclusions:**

The results of this study will determine the efficacy and acceptability of an mHealth intervention using behavior change techniques to promote health behaviors that support physical health and well-being in cancer survivors and will therefore have implications for health care providers, patients, health psychologists, and technologists.

**International Registered Report Identifier (IRRID):**

DERR1-10.2196/13214

## Introduction

### Background

In Ireland, an average of 37,000 new cases of cancer are diagnosed each year, and it is predicted that the incidence of cancer will double by 2040 [1]. At the same time, cancer survivorship in Ireland is increasing, with survival at 5 years from diagnosis having increased to 62% overall [1].

There is consistent evidence of a positive association between being overweight or obese and all-cause morbidity and mortality [2]. High body mass index (BMI), poor diet, and lack of physical exercise are identifiable risk factors for cancer development, and in cancer survivors, these factors can increase the risk of a secondary cancer or a subsequent primary cancer [3,4]. Cancer and cancer treatment can result in physical inactivity and loss of muscular strength [5]. Previous research has identified that approximately 50% of cancer survivors are overweight [6], and research in women has linked obesity to a 46% increased risk for eventual development of distant metastases [7]. Cognizant of the consequences of morbidity and mortality, there is a need to facilitate rehabilitation of cancer survivors to reduce BMI and improve physical and psychological health.

Mobile health (mHealth) is the practice of medicine and public health supported by mobile devices (eg, mobile phones, smartphones, tablets, mobile apps, and wearable monitors). The use of mobile apps has been associated with significant reductions in weight and BMI [8]. Mobile technology has also been shown to assist in behavior change for physical activity, and it offers much potential for sustainable lifestyle change, as it provides feedback to consolidate self-management habits [9,10]. Therefore, mHealth tools may help meet the need to provide cost-effective behavior change interventions that support weight loss.

Although mHealth interventions hold significant potential, adopting a theory and evidence-based approach to intervention design is critical [11]. The Behavior Change Wheel (BCW) is a synthesis of 19 frameworks of behavior change [12]. The BCW, together with the Behavior Change Technique (BCT) Taxonomy, a standardized list of the active ingredients of behavior change interventions [13], enables researchers to develop and describe complex interventions in a systematic and rigorous way.

Systematic review evidence suggests that the use of relevant BCTs significantly increased the success of weight loss programs [14]. A systematic review of existing healthy eating and physical activity interventions identified the BCTs *self-monitoring* in combination with *goal setting* and *feedback* as the most effective [15]. A recent meta-analysis of 30 randomized controlled trials (RCTs) to increase physical activity among cancer survivors reported that certain BCTs (*prompts*, *social rewards*, and *graded tasks*) were associated with larger increases in physical activity. Interventions using a greater number of BCTs were associated with greater physical activity gains [16]. As such, these BCTs should be considered for inclusion in interventions aiming to increase physical activity.

Studies have found that both mHealth interventions and the inclusion of relevant BCTs can lead to positive health behavior change and weight loss and therefore, gains may be particularly great when mHealth and BCTs are combined. Digital interventions including a greater number of BCTs were found to have larger effects on health behavior change than interventions with fewer BCTs [17]. A review and meta-analysis of studies using activity monitors found that in people with obesity, physical activity increases were greatest when the BCTs *goal setting* and *feedback* were incorporated in the mHealth intervention [18]. A systematic content analysis of the BCTs provided by wearable activity monitors concluded that most monitors included *self-monitoring*, *goal setting*, and *feedback* [19]. More generally, the review by Michie et al [15] found these to be the most effective BCTs for promoting healthy diet and physical activity.

mHealth interventions incorporating relevant BCTs have the potential to support weight loss [16,17,19]. However, there are a limited number of mHealth interventions using BCTs with cancer survivors. In the previously mentioned meta-analysis of 30 physical activity RCTs for cancer survivors [16], only 2 studies [20,21] used digital technologies as the mode of delivery (MOD) for BCTs to increase physical activity. The study by Bantum et al [20] found that a 6-week Web-based self-management workshop increased self-reported strenuous physical activity of cancer survivors. The other study with breast cancer survivors used *prompts* delivered by email in declining frequency over 12 weeks and reported significant group differences in self-reported physical activity levels postintervention [21]. These studies highlight that there is potential for digital health interventions to improve lifestyle behaviors among cancer survivors. Yet, more evidence is needed regarding the effectiveness of interventions using mobile technologies with cancer survivors on objective health outcomes.

### Aims and Objectives

The aim of this multidisciplinary research study is to investigate whether or not a personalized mHealth (mobile technology) self-management lifestyle program can improve physical and psychological outcomes of a subgroup of cancer survivors with increased health risks related to lifestyle behaviors. More specifically, this project will examine the impact of lifestyle advice and personalized goal setting compared with standard medical care on both clinical and psychological outcomes. Furthermore, this study will explore the acceptability of this intervention to participants receiving the Moving On program.

## Methods

### Study Design

A 2-arm, parallel, open-label RCT design was used to investigate the impact of a personalized mHealth intervention versus standard care on primary and secondary health outcomes. Eligible participants were randomized to either the intervention or the standard care control condition using a computerized random number generator. Assessments took place before randomization (T0; baseline), at 12 weeks (T1; intervention end), and at 24 weeks (T2; follow-up). The study was not blinded.

On completion of the study, a series of semistructured interviews were carried out to assess retrospective acceptability of the intervention from the perspective of the recipients. Purposeful maximum variation sampling was used. The theoretical framework of acceptability of health care interventions was used as a topic guide [22]. Specifically, open-ended questions were asked regarding participant’s affective attitude toward the intervention, the intervention’s coherence, participant burden, perceived effectiveness, and participants’ sense of self-efficacy.

### Study Setting

Recruitment and assessments took place in Letterkenny University Hospital, Co. Donegal, Ireland.

### Ethics Approval

The design of this study was approved by the National University of Ireland, Galway Research Ethics Committee on September 12, 2017 (Ref: 17/MAY/20), and by the Research Ethics Committee at Letterkenny University Hospital on May 2, 2017.

### Intervention

#### Development

The Moving On program is an intervention using BCTs and mobile technology to promote self-management of lifestyle behavior among cancer survivors who are overweight. The intervention was designed following the BCW [12] presented in Figure 1. The COM-B system at the center of the wheel proposes that people need the capability (C), opportunity (O), and the motivation (M) to perform a behavior (B). The second and third layers of the wheel describe intervention functions, the broad categories of means by which an intervention can change behavior, and policy categories that can support behavior change. The final step in intervention design is to identify BCTs and modes of delivery likely to be effective based on previous research.

Two behavioral targets were identified to improve health and well-being outcomes, which were to increase physical activity and improve diet. The functions of the first component of the intervention are *education* and *training*. The lifestyle information and education session aims to increase participants’ psychological capability to change behavior by imparting knowledge and skills to increase healthy eating and exercise. The function of the second intervention component (goal setting) was *enablement*. Participants were provided with a Fitbit activity tracker influencing their opportunity to increase physical activity. Participants also received short message service (SMS) text messaging contact from the behavioral science researcher regarding physical activity goals aiming to influence their motivation to increase exercise.

**Figure 1 figure1:**
[figure not shown]
The behavior change wheel reproduced with permission from Michie et al.

Next, a detailed intervention plan was developed and described using the BCT Taxonomy version 1 [13]. Key BCTs were selected on the basis of successful application in previous interventions targeting physical activity and dietary behavior change [14-16,18]. The full intervention specification detailing the content (BCTs) and MOD [23] for each BCT are described for both components of the intervention in Tables 1 and 2. The lifestyle information and education session was delivered primarily through face-to-face human contact in real time to groups of participants. In contrast, the goal setting intervention was delivered through human contact at a distance using nonautomated SMS text messages and facilitated using digital wearable technology.

**Table 1 table1:** Description of intervention content of the lifestyle information and education session (week 1) specified in terms of the Behavior Change Technique Taxonomy Version 1 and the Mode of Delivery Taxonomy.

BCT^a^ and definition	Application in this study
Goal setting (outcome): set or agree on a goal defined in terms of a positive outcome of wanted behavior.	All participants enrolled in the research study are encouraged to lose weight by increasing their level of physical activity and improving their diet; MOD^b^: human and face-to-face.
Provide information on consequences of behavior to the individual: provide information (eg, written, verbal, and visual) about health consequences of performing the behavior.	Participants are given information on physical activity and healthy eating tailored to cancer survivors. For example, that high-impact activity, such as walking, is safe for cancer survivors.
Demonstration of the behavior: provide an observable sample of the performance of the behavior.	A series of physical exercises are demonstrated by the physiotherapist, and participants are shown how to use body parts (eg, hand) as a visual guide for healthy portion size. Information is summarized in a written information sheet to take home; MOD: human and face-to-face; MOD: printed material and leaflet
Provide instruction on how to perform the behavior: advise or agree on how to perform the behavior.	A series of physical exercises are demonstrated by the physiotherapist, and participants are shown how to use body parts (eg, hand) as a visual guide for healthy portion size. Information is summarized in a written information sheet to take home; MOD: human and face-to-face; MOD: printed material and leaflet
Problem solving: analyze, or prompt the person to analyze, factors influencing the behavior and generate or select strategies that include overcoming barriers and/or increasing facilitators.	Using a worksheet, each participant is prompted to record their goal, identify barriers to their goal, define the barrier in terms of it being a personal, environmental, social, or organizational barrier, and finally to identify strategies to overcome each barrier identified; MOD: human and face-to-face
Goal setting (behavior): set or agree on a goal defined in terms of the behavior to be achieved	Participants agree to gradually increase their physical activity level, including their average daily step count
Action planning: prompt detailed planning of performance of the behavior, must include at least 1 of context, frequency, duration, and intensity	Each participant is prompted to make a plan to increase their physical activity level toward the recommended 10,000 steps per day and perform the exercises recommended by the physiotherapist at a time/place of their choosing from a choice of schedules; MOD: human and face-to-face

^a^BCT: behavior change technique.

^b^MOD: mode of delivery.

**Table 2 table2:** Description of intervention content of the goal setting intervention (weeks 4-12) specified in terms of the Behavior Change Technique Taxonomy Version 1 and the Mode of Delivery Taxonomy.

BCT^a^ and definition	Application in this study
Self-monitoring of behavior: establish a method for the person to monitor and record their behavior(s) as part of a behavior change strategy	Participant is provided with a Fitbit Alta activity tracker. Physical activity behavior is visually displayed on the screen, and a log of their previous activity is recorded and displayed on the app interface; MOD^b^: digital, wearable, and accessory; MOD: digital, phone, and app
Feedback on behavior: monitor and provide informative or evaluative feedback on performance of the behavior and must include one of form, frequency, duration, and intensity.	Once a week, the participant is contacted by SMS^c^ text messages to inform them of their average daily step count; MOD: human, distance, and SMS text message
Goal setting (behavior): set or agree on a goal defined in terms of the behavior to be achieved	Participant is contacted by SMS text messages with a daily step count goal for the following week; MOD: human, distance, and SMS text message
Graded tasks: set easy-to-perform tasks, making them increasingly difficult, but achievable, until behavior is performed	The participants’ step count goal is calculated by adding 10% to their previous week’s average daily step count and sent by SMS text messages; MOD: human, distance, and SMS text message
Social reward: arrange verbal or nonverbal reward if and only if there has been effort and/or progress in performing the behavior (includes *positive reinforcement*)	The participant receives a congratulatory SMS text message if they successfully achieve their step count goal that week; MOD: human, distance, and SMS text message
Review behavior goal(s): review behavior goal(s) jointly with the person and consider modifying goal(s) or behavior change strategy in light of achievement	If the participant does not successfully achieve their step count goal, a new goal is calculated based on their previous week’s activity level and sent by SMS text messages; MOD: human, distance, and SMS text message

^a^BCT: behavior change technique.

^b^MOD: mode of delivery.

^c^SMS: short message service.

#### Description

The intervention had 2 components: (1) a lifestyle information and education session delivered by health professionals (specifically, 3 physiotherapists, 1 dietician, and 1 clinical psychologist) at Letterkenny University Hospital and (2) goal setting intervention delivered by a behavioral science researcher using mobile technology.

##### Lifestyle Information and Educational Session (Week 1)

Participants in the intervention group attended a 1-day (4-hour) session in small groups of 10 to 15 people, where they received personalized and tailored lifestyle information from physiotherapists, a dietician, a clinical psychologist, and a behavioral scientist. Participants received a comprehensive presentation from each specialist. The physiotherapists demonstrated a series of daily strengthening exercises that were suitable and safe posttreatment. Moderate physical activity for 30 min 6 days a week, 45 min 4 days a week, or 10 min 2 times a day was recommended. Participants were advised to choose a personal activity schedule that best fit their lifestyle. Their preference or adherence to a particular schedule was not measured or controlled. The behavioral science researcher prescribed a weekly increase of 10% in average daily step count over the course of the program. The dietician advised participants to reduce their calorific intake, reduce red meat, processed meat, salt and sugar, and increase fruit, vegetable, and fiber intake. Participants were provided with an information sheet to take home summarizing the key messages from the lifestyle information and education session and booklets by the World Cancer Research Fund on healthy eating and physical activity. The BCTs included in this session are shown in Table 1.

##### Goal Setting Intervention (Weeks 4-12)

Participants in the intervention group self-monitored their physical activity using their Fitbit. In addition, participants in the intervention group were contacted by the behavior specialist through SMS text messages on weeks 4 to 11 to provide feedback on their average daily step count, review physical activity goals, and set graded tasks (increase daily step count by 10%). Participants gradually increased their physical activity (+10% each week) toward the recommended 10,000 steps per day. Participants continued to self-monitor their progress for the remaining 3 months of the study without review/feedback from the behavior specialist. The BCTs included in the goal setting intervention are presented in Table 2.

##### Materials

Each participant was provided with a Fitbit activity tracker and registered with a Fitbit user account. The Fitbit is an accelerometer-based device that is worn on the wrist. The intervention group wore the Fitbit Alta to track health outcomes. Summary data (eg, step count and active minutes) were visible on the device display, and additional data (eg, sleep data) were available on the Fitbit app dashboard.

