##### Materials

All participants in the control group were provided with Fitbit Flex 2 to track health outcomes. The display panel on this device does not present summary data (ie, step count and number of active minutes), and the application dashboard was modified to not display summary data.

On being recruited to the study based on meeting the eligibility criteria (BMI ≥25 kg/m^2^), all participants were encouraged to lose weight (ie, BCT; *goal setting [outcome]*) because of health care professionals’ duty of care. Participants in the control group attended a 15-min session in small groups of 10 to 15 participants, where they received a Fitbit Flex 2. In addition, as in standard medical care, there was provision of health information at this session (ie, BCT *information on consequences of behavior to the individual*, but not BCT *instruction on how to perform the behavior* or *demonstration of the behavior*). Therefore, leaflets were made available, and standard advice was available from oncology nursing staff on request. No further information was given at this time. Finally, participants in the control group wore the Fitbit Flex 2 for monitoring their physical activity, but without *goal setting (behavior)*. The visual display on the device and the app limited but did not eliminate their ability to *self-monitor* behavior.

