### Procedure

A flow diagram of the progress through each phase of this 2-group parallel randomized trial is presented in Figure 2. A total of 123 eligible participants attended baseline assessments. Participants were randomized to the control or intervention arm. Of 123 participants, 62 assigned to the intervention group were invited to attend a lifestyle information and education session where they would also receive their Fitbit activity monitor, and 55 were able to attend. During the lifestyle information and education session, each participant was provided with a Fitbit Alta. The Fitbit activity tracker was set up and paired with the participants’ mobile device. The participant was given an information sheet with instructions on how to synchronize their Fitbit device and app and asked to perform this weekly.

The remaining 61 participants assigned to the control group were invited to an appointment where they would be provided with a Fitbit activity monitor, and 53 were able to attend. During this meeting, each participant was provided with a Fitbit Flex 2. The Fitbit was paired with the participants’ mobile device. The participant was given an information sheet with instructions on how to synchronize their Fitbit and asked to perform this weekly or at least once a month to prevent loss of data.

All participants wore a Fitbit® activity monitor for the 6-month duration of the study. Participants in the intervention group received weekly personalized SMS text messages, including feedback on their physical activity level and a personalized physical activity goal each week for 8 weeks.

All participants were invited to a postintervention assessment (12 weeks later) to determine efficacy of the lifestyle information and education session and personalized goal setting mHealth intervention for increasing physical activity and improving clinical and psychological outcomes.

All participants continued to wear Fitbit for the remainder of the study, but the personalized goal setting intervention had ceased after 12 weeks. To determine if any effects of a lifestyle information and education session and personalized goal setting mHealth intervention were maintained 3 months later, all participants were invited to a follow-up assessment (6 months after baseline assessment).

At the conclusion of the study, all participants in the intervention group were invited to be interviewed about their experience of the Moving On program, and 13 interviews were conducted.

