#### Health Behavior Outcomes

Self-reported physical activity level was measured using the 4-item Godin Leisure-Time Exercise Questionnaire [33]. Respondents rate the frequency of 15-min bouts of strenuous, moderate, and mild exercise in a 7-day period. Participants also rate how often they engage in regular activity sufficient to break a sweat (1 often, 2 sometimes, and 3 never). Higher scores indicate higher subjective physical activity.

Objective physical activity level (ie, average daily step count) was measured continuously using the Fitbit activity tracker.

Dietary data were collected using the European Prospective Investigation into the Cancer and Nutrition (EPIC) Norfolk Food Frequency Questionnaire (FFQ) [34]. Participants were asked to report the frequency of 130 different foods and beverages consumed over the previous 3 months. The FFQ EPIC Tool for Analysis [35] provides estimates of 10 food groups.

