### Statistical Analysis

To maximize power and conform to intention-to-treat analysis, missing data will be handled using multiple imputation methods (ie, the expectation-maximization algorithm) if assumptions regarding mechanisms of missingness are met.

A series of 3 (baseline, T1, and T2) × 2 (control and intervention) mixed ANOVAs will be performed to determine the efficacy of a lifestyle information and education session and goal setting mHealth intervention on clinical, psychological, and health behavior measures.

Independent sample *t*-tests will be used to analyze group differences (control and intervention) in average daily step count across the 24 weeks of the study.

Thematic analysis of interview transcripts will be used to explore the acceptability of the Moving On program for recipients.

Quantitative data will be analyzed with IBM SPSS Statistics 24. NVivo 12 will be used to facilitate organization and analysis of qualitative data.

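### Tracker model coincides with trial arm and no step count precedes randomization, so the planned t-test on steps cannot separate a device counting difference from a difference in walking

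*Protocol article*

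**What the plan says.** The Materials paragraph under the intervention description states: "The intervention group wore the Fitbit Alta to track health outcomes". Its counterpart under Control Condition states: "All participants in the control group were provided with Fitbit Flex 2 to track health outcomes". Health Behavior Outcomes defines the outcome: "Objective physical activity level (ie, average daily step count) was measured continuously using the Fitbit activity tracker". Statistical Analysis then says that independent-samples t-tests "will be used to analyze group differences (control and intervention) in average daily step count across the 24 weeks of the study".

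On timing, Study Design says: "Assessments took place before randomization (T0; baseline), at 12 weeks (T1; intervention end), and at 24 weeks (T2; follow-up". Procedure places the hand-out of trackers after that point. For the intervention arm: "During the lifestyle information and education session, each participant was provided with a Fitbit Alta". Controls received theirs at a separate appointment, also after randomization. Of those randomized, 55 of 62 intervention and 53 of 61 control participants attended the session at which trackers were given out.

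The article explains why the control device differs: the Flex 2 does not show summary data, and the app was modified to match, so that self-monitoring was limited in that arm. It reports no agreement data between the two models, no calibration, no common second tracker and no sensitivity analysis for device.

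**The concern.** Every tracker wearer in one arm has one model and every wearer in the other arm has the other. A systematic difference in how the models register steps would therefore enter the between-arm difference in full. Randomization gives no protection, because the device was assigned together with the arm. A device term cannot be fitted either, because it would be the same variable as treatment. A pre-randomization step count on each person's own tracker would have allowed a partial correction, but none is described.

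Step count is the outcome that the article labels objective physical activity. If the models count differently, a significant result could be partly or wholly a measurement artefact. An offset in the other direction could mask a real gain in walking.

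**Working it through.** **Structure.** Intervention equals Alta and control equals Flex 2. If D is the true difference in mean daily steps and B the counting offset between models, the t-test estimates D + B. With model and arm perfectly aligned, and without a pre-randomization step count, the planned data cannot separate D from B.

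**No stated figure to reproduce.** The article gives no sample size or power for the step-count test. Its figure of 102 is for the repeated-measures ANOVA and has no bearing here.

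**Inputs.** From Procedure: 53 control and 55 intervention participants at the sessions where trackers were given out. Assumed, because the article does not give them: two-sided alpha of 0.05, and the offset B in SD units of daily steps.

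**Formula.** With no true effect, the t statistic follows a noncentral t distribution with 53 + 55 − 2 = 106 degrees of freedom and noncentrality B / sqrt(1/53 + 1/55). The denominator is sqrt(0.01887 + 0.01818) = 0.1925.

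| Assumed offset (SD) | Noncentrality | Probability of a significant result |
|---|---|---|
| 0 | 0 | 5.0% |
| 0.05 | 0.26 | 5.8% |
| 0.10 | 0.52 | 8.1% |
| 0.20 | 1.04 | 17.8% |
| 0.30 | 1.56 | 33.9% |
| 0.50 | 2.60 | 73% |

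**The same on a proportional scale.** Assume a mean of 7,000 steps and an SD of 2,500 to 3,500 (neither is in the article). An offset of proportion b is b × 7,000 / SD in SD units; for example, 0.10 × 7,000 / 3,000 = 0.233. False-positive rates are then 5.5–6.0% for a 2% offset, 8–11% for 5%, 18–30% for 10% and 54–82% for 20%.

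**Masking.** The same function gives power. A true effect of 0.50 SD has 73% power without an offset. With an opposing offset of 0.20 SD the net difference is 0.50 − 0.20 = 0.30 SD, and power falls to about 34%.

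**Scale.** The difference detectable with 80% power is (1.960 + 0.842) × 0.1925 = 0.54 SD. An observed difference of that order would exceed a small offset but might not exceed a large one.

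**The case against.** The strongest reply is that the article documents no offset at all. It describes the Fitbit generically as a wrist-worn accelerometer, and if both models count alike the test keeps its 5% error. The choice of device is also purposeful: self-monitoring is a listed intervention component, and the Flex 2 limits it in controls. Step count is one of many outcomes, and an unseen analysis plan may address device.

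Much of this stands. The display difference belongs to the treatment contrast and is not a fault. It does not follow that the models count equally, and the article fixes both the devices and the test without addressing that.

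Three stronger readings are tempting and are not supported:

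- **That the comparison cannot show an intervention effect.** This would need a known, material offset. A difference clearly larger than a justified bound on the offset would still be evidence.
- **That less frequent syncing caused more data loss in controls.** Controls were "asked to perform this weekly or at least once a month to prevent loss of data". The article presents syncing at least monthly as enough to avoid loss, and reports no loss that differs by arm.
- **That the t-test should give way to change from weeks 1–3, or to the walk test and Godin score.** Weeks 1–3 are not a baseline. Education, an agreed step goal, action planning and a visible step display all begin with the week 1 session. The walk test measures exercise capacity, and Godin is self-report in an unblinded trial.

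**Conclusion.** The point holds in limited form. Device model is perfectly aligned with arm, and no pre-randomization step count is described. The t-test "in average daily step count across the 24 weeks of the study" therefore estimates the walking difference plus any counting offset. A step difference is not attributable to the intervention without evidence bounding that offset, and the article describes none.

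The size is conditional. Over assumed offsets of 0 to 0.30 SD the false-positive rate runs from about 5% to about 34%; the direction is unknown, so a real effect could equally be hidden. These figures rest on 53 and 55 analysed participants, two-sided 5% testing, and an offset that shifts the mean without changing the spread. Other outcomes use the same instruments in both arms and are not affected by this problem.

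**What to change.** Keep the t-test and add the following:

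1. A tipping-point sensitivity analysis. Rescale one arm's step counts over a stated range of proportional device offsets, in both directions and including zero. Repeat the test at each value, and report the offset at which the conclusion changes.
2. A statement in the analysis and the conclusions that device model equals arm. Attribute a step difference to the intervention only if it exceeds a bound on the offset, with the source of that bound given (for example, agreement data from both models worn together).
3. If within-person change from weeks 1–3 is shown, label it secondary. It assumes a constant proportional offset, removes early effects of education, goal setting and self-monitoring, and mainly reflects the added text-message feedback. It should not replace the main comparison.
4. Treat the walk test and Godin score as supportive only.

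The article reports data collection complete and analysis underway, so this needs only analysis and wording. The price is slightly more analysis and a more cautious step-count conclusion.
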